## Abstract

Disruptions in cognitive function have been reported in individuals undergoing haemodialysis and those with chronic kidney disease. This pilot study protocol primarily assesses the feasibility and acceptability of using mobile cognitive gaming apps for patient-led cognitive training during haemodialysis sessions. The protocol consists of three phases: (1) reviewing and evaluating available cognitive gaming apps, (2) conducting focus groups/interviews with people with kidney disease to determine app preferences, and (3) undertaking a quasi-experimental randomised controlled trial to compare cognitive outcomes between a patient-led app intervention group and a standard care control group over four months. Primary outcomes will include changes in cognitive test scores [Montreal Cognitive Assessment (MoCA), Modified Mini-Mental State Exam (3MSE), Rapid Objective Working Memory Assessment (ROWMA)], while secondary outcomes will encompass quality of life measures [Patient-Reported Outcomes Measurement (PROM) Kidney Disease Quality of Life Short Form (KDQoL-SF™) v 1.3, Patient-Reported Outcomes Measurement Information System (PROMIS) Global Health Instrument, European Quality of Life Five Dimension (EQ-5D)]. If demonstrated to be effective, this novel method of utilising gamified cognitive training applications could potentially mitigate cognitive decline and improve the well-being of people receiving haemodialysis without necessitating significant clinical resources. The findings from this research will guide the development of a larger definitive randomised trial in the future.

## Introduction

Cognitive impairment is a significant issue among people with chronic kidney disease (CKD) and people receiving haemodialysis. The CKD-related effect on cognition increases with CKD stage progression and occurs on top of the normal age-related cognitive impairments^1^. Disruptions in cognitive function, characterised by a decline in performance in one or more cognitive domains such as memory, attention, and executive functioning, have been widely reported in the CKD population compared to the general population^2–4^. The prevalence of cognitive deficits in one or more domains ranges from 16–38% depending on the stage of CKD^5–8^. People receiving haemodialysis have anecdotally reported experiencing a ‘brain fog’ with impairments in cognitive function, including memory, thinking, and concentration^9–11^.

Despite the significant impact of cognitive impairment on the quality of life and well-being of people with CKD, there is often a lack of awareness and engagement in addressing this issue^12^. Less than 5% of people with CKD have been evaluated and diagnosed for cognitive impairment, highlighting a substantial gap in recognising and treating cognitive deficits in this population^13–15^. Given the lack of awareness and engagement in addressing cognitive impairment in people with CKD, there is a need for innovative and accessible interventions to mitigate cognitive decline in this population.

Cognitive brain training is a non-pharmacological intervention in which participants undertake a series of cognitive activities with the goal to preserve or enhance their mental abilities, including memory, attention, judgment/decision-making, learning and reasoning^16^. A recent study in people receiving haemodialysis and cognitive training using a classical n-back memory task showed improvements in cognitive and attentional function^17^. The n-back task involves monitoring a sequence of stimuli and identifying when the current stimulus matches the one from n steps earlier in the sequence. It is designed to assess and train working memory and cognitive control by requiring participants to update and maintain relevant information over varying periods of time^18^. However, one problem with such specialised cognitive training tasks is that they can be disengaged to the person as they are repetitive, frustrating and effortful and are typically required to be delivered by a health professional/researcher, thus adding significant resource implications.

Traditional cognitive training tasks often lack engaging elements and require significant effort from the patient, leading to low adherence and high dropout rates^19^. Moreover, the need for delivery by trained professionals limits accessibility and increases resource burdens on healthcare systems^20,21^. In contrast, gamified cognitive training apps offer an accessible, engaging, and self-directed approach to cognitive rehabilitation. By incorporating game design elements such as rewards, challenges, and personalized feedback, these apps can enhance motivation, adherence, and overall user experience. The self-directed nature of gamified apps also reduces the need for direct supervision by healthcare professionals, potentially increasing scalability and cost-effectiveness of cognitive interventions^22^.

A recent approach to cognitive rehabilitation is the use of digital mobile gaming apps delivered via smartphones and tablet devices^23^. Such gamification apps have advantages in terms of adding elements of fun and enjoyment, thereby empowering patients to engage and adhere much more to cognitive rehabilitation tasks. In addition, by tapping into users’ appetite for healthy competition, gamification apps can increase compliance and personal motivation levels. It may also potentially make positive use of the time spent on haemodialysis and have secondary beneficial impacts on carers and family. An investigation by Bento et al. has shown that a digital therapeutic game intervention improved depressive symptoms in elderly patients undergoing haemodialysis treatment^24^. Additionally, McAdams-DeMarco et al. found that playing tablet-based brain games during haemodialysis may prevent cognitive decline^25^. More recently, it has been shown that intradialytic cognitive training interventions can improve functional status of people undertaking haemodialysis^26,27^. There are brain gaming apps available that provide cognitive training (recalling information, attention, problem-solving, and mental agility) and have the potential to be utilised to prevent the decline in cognitive function during haemodialysis^28^. Patient-led cognitive gamified training (CGT) refers to the use of gamified cognitive training apps by patients independently, without direct supervision or guidance from healthcare professionals. This approach empowers patients to engage in cognitive rehabilitation at their own pace and convenience, potentially increasing adherence and effectiveness.

## Research question

The primary research question is: Is it feasible to implement patient-led CGT interventions delivered through smartphone/tablet-based gaming apps during haemodialysis sessions, and what is the potential impact on cognitive function, quality of life, well-being, and functional capacity in people with CKD undergoing haemodialysis?

## Aims and objectives

The overall aim of this trial protocol is to utilise smartphone/tablet-based gaming apps to deliver patient-led CGT during haemodialysis sessions without the direct involvement of health professionals. The specific trial aims are:

To investigate the effect of patient-led CGT intervention on cognitive decline during haemodialysis.To utilise smartphone/tablet-based gaming apps to deliver patient-led CGT during haemodialysis sessions without the direct involvement of health professionals.To assess the quality of life, well-being, and functional capacity of people receiving haemodialysis at baseline and the end of the trial.

To achieve these aims, our objectives are to:

Identify and classify which cognitive apps and games can be used by people with CKD during haemodialysis sessions.Develop a CGT intervention for the haemodialysis sessions of people with CKD.Develop an understanding of how patient-led CGT during haemodialysis sessions affect:Cognitive decline of people with CKD who undergo haemodialysis therapy, as cognitive function is a key outcome of interest and may be positively influenced by the intervention.Quality of life, well-being and functional capacity of people with CKD who undergo haemodialysis therapy, as these factors are important patient-centred outcomes that may be indirectly impacted by improvements in cognitive function and the engaging nature of the intervention.

## Methods and analysis

### Trial design

This trial is a single-centre, two-armed pseudo-randomised controlled pilot trial to assess the feasibility and effectiveness of patient-led CGT intervention for slowing cognitive decline in people receiving haemodialysis. This trial will contain three phases. Phase one will conduct a review and evaluation of CGT apps in the marketplace. The outcome of Phase one is to have a shortlist of CGT apps for the next phase by evaluating cognitive training apps. Phase two will assess and select CGT apps for the intervention phase by conducting semi-structured interviews with the haemodialysis patient focus group involving representatives from the Kidney Patient Associations (KPAs), people with kidney disease, and Kidney Care UK. Phase three will be a pseudo-randomised controlled study in which people receiving haemodialysis will undertake CGT intervention by engaging CGT apps during haemodialysis sessions. The outcome of Phase three will be to have comparisons of baseline and four-month follow-up assessments between the intervention group, which receives CGT apps, and the control group, which only has standard care. The trial flow diagram is presented in Fig. 1.

**Fig. 1 Fig1:**
[figure not shown]
The trial flow diagram.

### Intervention timeline

The CGT intervention will be delivered during the first half of the haemodialysis session, typically within the first 1–2 h, to ensure that patients are alert and able to engage with the cognitive training. Regarding the study procedures:

Baseline assessments (questionnaires and cognitive tests) will be conducted in the week prior to starting the intervention.The intervention will last for four months (16 weeks ± two weeks).Patients will be asked to use the cognitive training apps for approximately 30 min during each haemodialysis session, 3 times per week.Post-intervention assessments will be conducted in the week following completion of the 16-week intervention.

### Intervention implementation and practical considerations

Participants will be instructed to use their non-fistula/graft arm for interacting with the tablet during CGT to avoid any potential complications. All tablets will have stands to minimise arm movement if required.

Regarding the timing of dialysis shifts, we acknowledge that early morning shifts may pose challenges. To address this, we will ensure that the CGT apps are designed with adjustable brightness and volume settings to accommodate patient comfort at different times of day.

The involvement of dialysis staff will be minimal to ensure the intervention remains patient-led. Staff responsibilities will include:

Initial setup of tablets (performed by the research team).Providing tablets to patients at the start of their session.Basic troubleshooting if needed (e.g., restarting an app).Collecting tablets at the end of the session.

Staff will receive a brief training session on these responsibilities. We estimate this will require no more than 5–10 min of staff time per patient per session. The research team will be available to address any technical issues that arise.

### Trial population and recruitment

The investigators will collaborate with local representatives of KPAs and people within the kidney service to recruit the participants who are currently receiving haemodialysis therapy at the Hull University Teaching Hospitals NHS Trust kidney service. Healthcare professionals at the kidney unit will discuss study participation with the patients before obtaining formal informed consent.

The investigators will give potential participants a letter and the trial participant information sheet. Consent for participation in the trial will be collected via a formal Informed Consent Form authored by the investigators; the consent form will check candidates suitability against both inclusion and exclusion criteria (fit recruitment profile/ confirmation that situations have not changed since recruitment), and outline the specifics of the trial, what activity is included in the intervention sessions (methodology outline) and how both feedback and personal data will be collected and processed. All inclusion and exclusion criteria are given in Table 1. For Phase two, the focus group/semi-structured interview sessions will be conducted with people who meet the same inclusion and exclusion criteria as the main trial participants (Table 1), ensuring consistency in the target population.

**Table 1 Tab1:** Inclusion and exclusion criteria of the proposed trial.

Inclusion criteria	Exclusion criteria
18 years or older	Less than 18 years of age
regular haemodialysis therapy for at least three months	Haemodialysis for less than three months
	Planned kidney transplant within the intervention period
	Active malignancy
	Inability to complete study assessments from the clinical perspective
	Inability to complete the interventions from the clinical perspective
	Inability to use tablet and the CGT app Inability to consent to study

As this is a pilot study, the sample size is determined by the number of eligible patients in the participating haemodialysis unit. While formal age-matching between the intervention and control groups is not feasible due to the small sample size, we will strive for balance in baseline characteristics through randomisation. The primary aim of this pilot study is to assess feasibility and gather preliminary data to inform a future, larger randomised controlled trial.

### Participant withdrawal

Participants have the right to withdraw from treatment and/or the trial at any time. Participants will remain in the trial for follow-up unless they request to fully withdraw. All data up to the point of withdrawal will be stored, after withdrawal participant’s data will be destroyed and will not be included in the final dataset.

In the event of participant withdrawal, the Investigator(s) will promptly explain to the participant that their involvement in the trial will discontinue and explain why.

For Phase two, the focus group/semi-structured interview sessions will be conducted with people who are currently receiving haemodialysis therapy. After receiving feedback from the focus groups/semi-structured interviews, a finalist of CGT apps will be determined to be used during haemodialysis sessions.

Fifty-five people attending haemodialysis therapy will be recruited for Phase three. The intervention arm includes 30 patients to account for up to a 20% potential dropout and ensure at least 25 can complete the study. The control arm will have 25 haemodialysis patients with usual care. All participants will complete assessments at baseline and at approximately four months (± two weeks).

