Rapid Objective Working Memory Assessment (ROWMA)	Assesses working memory	Scores vary; higher scores indicate better working memory function	Baseline and 4 months	5–10 min	Computerised test
Kidney Disease Quality of Life Short Form (KDQoL-SF™)	Kidney disease-specific quality of life measure	0-100 for each subscale; higher scores indicate better quality of life	Baseline and 4 months	10–15 min	Includes generic and kidney disease-specific components
PROMIS Global Health Instrument	Brief measure of general health-related quality of life	T-score metric (mean = 50, SD = 10); higher scores indicate better health	Baseline and 4 months	5–10 min	Assesses physical, mental, and social health
European Quality of Life 5-D (EQ-5D)	Generic measure of health status	Index value 0–1; higher scores indicate better health status	Baseline and 4 months	5–10 min	Provides health utility scores for economic evaluations

*Score ranges and interpretations are based on general population normative data unless otherwise specified. Specific cutoff values and interpretations for the haemodialysis population may differ and are currently not well established. This highlights the exploratory nature of using these assessment tools in our specific.

Examining and comparing the cognitive and behavioural test scores of the intervention and control groups at the four-month assessments will provide insight to expand the scope and area of CGT intervention to other haemodialysis units. Feasibility outcomes will include patient recruitment and retention rates, adherence to the intervention (app usage frequency and duration), and the occurrence of any technical issues or adverse events. Acceptability will be assessed through semi-structured interviews with a subset of intervention group participants, exploring their experiences, satisfaction, and perceived benefits and challenges of using the CGT apps. If the feasibility and acceptability of CGT intervention are demonstrated, we will apply for further funding so that the CGT intervention can be delivered to more people receiving haemodialysis.

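### The withdrawal rule both keeps and destroys the data of participants who fully withdraw, so their app-usage, technical-issue, adverse-event and baseline records may be lost

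*Protocol article*

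**What the plan says.** The Participant withdrawal section contains three relevant statements.

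- Reach: "Participants will remain in the trial for follow-up unless they request to fully withdraw". Stopping the intervention and leaving the trial are therefore different events, and only the second ends data collection.
- Storage: "All data up to the point of withdrawal will be stored".
- Destruction, in the same sentence as the storage clause: once someone has withdrawn, that person's "data will be destroyed and will not be included in the final dataset".

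The same section sets the only attrition figure in the plan: "The intervention arm includes 30 patients to account for up to a 20% potential dropout and ensure at least 25 can complete the study". No such allowance is given for the 25 controls.

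The Outcomes section defines what the pilot must measure on feasibility: "Feasibility outcomes will include patient recruitment and retention rates, adherence to the intervention (app usage frequency and duration"), and also "the occurrence of any technical issues or adverse events". The Trial population and recruitment section ranks this purpose first: "The primary aim of this pilot study is to assess feasibility and gather preliminary data to inform a future, larger randomised controlled trial". The Statistical analysis section gives the same emphasis when it explains why there is no power calculation.

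**The concern.** The storage and destruction clauses give opposite instructions for the same records. Staff who follow the second clause would delete everything held on a participant who leaves the trial: baseline scores, app-usage logs, reported technical faults and adverse events. Deletion cannot be undone, so no later analysis plan could repair it.

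The loss would be selective. Someone who leaves the trial altogether is plausibly more likely than others to have used the app little, met technical trouble or had an adverse event. Those are the observations the feasibility outcomes exist to capture, and they are meant to inform the design of a larger trial. Without the baseline records, nobody could compare leavers with those who stayed.

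**Working it through.** **The plan's own figure.** The intervention arm is 30, to leave at least 25 completers with up to 20% dropout. Adding 20% to 25 gives 25 × 1.20 = 30, which reproduces the stated number. (Dividing instead gives 25 / 0.80 = 31.25, rounded up to 32. Also, 20% of 30 is 6, leaving 24 rather than 25. That is a separate matter and does not affect this point.)

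**The two clauses side by side.**

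1. First clause: records made before withdrawal are kept.
2. Second clause: after withdrawal, the participant's data are destroyed and left out of the dataset. The clause does not limit this to data collected afterwards.
3. The preceding sentence keeps everyone else in follow-up, so the rule matters only for full withdrawals. The section also says that involvement in the trial ends on withdrawal, so little or nothing would be collected later.
4. If the second clause covered only later data, it would have almost nothing to act on. If it covers all the participant's data, it cancels the first clause. Neither reading makes the sentence work as written.
5. No other section exempts usage, event or baseline records from destruction.

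**How many participants.** The allowance is up to 0.20 × 30 = 6 intervention participants. The protocol does not divide dropout into full withdrawal, stopping treatment only, or other causes. The number affected at the allowance is therefore k = 0 to 6.

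**Effect on adherence (illustration).** The documents give no adherence figures, so these are assumptions:

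- c = mean share of scheduled sessions used by participants whose records remain, 70% to 90%;
- d = mean share used by those who fully withdrew, counted over all scheduled sessions, 10% to 50%.

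The schedule is 3 sessions a week for 16 weeks, or 48 sessions, so 10% to 50% means roughly 5 to 24 sessions.

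- Adherence with all 30 counted: [(30 − k)c + kd] / 30.
- Adherence after deletion: c.
- Overstatement: k(c − d) / 30.

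| k | smallest gap (c = 70%, d = 50%) | largest gap (c = 90%, d = 10%) |
|---|---|---|
| 0 | 0 points | 0 points |
| 1 | 0.7 points | 2.7 points |
| 3 | 2 points | 8 points |
| 6 | 4 points | 16 points |

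For example, with k = 6, c = 90% and d = 30%, adherence over all 30 is (24 × 0.90 + 6 × 0.30) / 30 = 78%, but it would be reported as 90%.

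No comparable figure can be given for technical issues or adverse events, because the documents state no rates. Any such event in a deleted record would simply not appear.

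**The case against.** The strongest defence is that a sentence should be read so that both halves have effect: keep what was collected before withdrawal, and discard anything that arises afterwards. That may be what was meant, and it is close to the fix below. But the text does not say it, and the cost of the other reading is irreversible. The sentence needs rewording on either reading.

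The limits on the consequences are sound, and three stronger inferences should not be drawn.

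- *That everyone who abandons the app disappears.* A participant who finds the apps tiring or unworkable can stop treatment and remain in follow-up. Only full withdrawals are reached, and nothing shows that all six allowed dropouts would be of that kind.
- *That dropouts vanish from the retention rate.* The plan fixes recruitment at 55 (30 and 25) and nowhere says that retention is computed from the final dataset alone. A count of withdrawals may survive in recruitment records. At the allowance, retention would still be 24/30 = 80%.
- *That the sentence biases the cognitive comparison.* A fully withdrawn participant has no four-month score whether or not the baseline is kept. That missing-outcome bias exists under either rule, and the fix does not remove it. Keeping the baseline only allows leavers to be described.

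The consent form, which is to set out how personal data are processed, is not shown. If it promised deletion, a new protocol sentence cannot override that promise for people already enrolled.

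**Conclusion.** The point holds in a limited form. The withdrawal sentence contradicts itself. On its plain reading it destroys the usage, technical-issue, adverse-event and baseline records of participants who fully withdraw, which favours the adherence, technical-issue and adverse-event results.

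At the plan's 20% allowance this concerns at most 6 of 30 intervention participants, and possibly none. The 4 to 16 point overstatement of adherence applies only if all six withdraw fully and the assumed usage rates are about right; with fewer full withdrawals it shrinks in proportion. It also assumes that adherence is counted over all scheduled sessions. The contradiction itself rests on no assumption. Because deletion is irreversible and bears on the pilot's stated primary aim, the sentence should be corrected before it is applied to anyone.

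**What to change.** Replace the sentence with: 'Data collected up to the point of full withdrawal will be retained and analysed in the participant's allocated arm; no further data will be collected afterwards.'

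Then:

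- use all consented participants as the denominator for retention and adverse events, and all consented intervention-arm participants for adherence;
- keep the number, timing and, where given, reason of withdrawals by arm;
- treat erasure as distinct from full withdrawal: erase data only where a participant separately and explicitly asks for it, or where consent already given promised deletion, and report the number of erasures by arm.

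The cost is an ethics amendment with matching wording in the information sheet and consent form. No extra data are collected. Anyone already enrolled under a promise of deletion stays under it, so some loss may remain, and the reported number of erasures will show how much.

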### Statistical analysis

Given the pilot nature of this study, our sample size is not based on formal power calculations. Instead, it is pragmatically determined by the number of eligible patients in our dialysis unit. The results will be used to estimate effect sizes and inform sample size calculations for a future, full-scale randomised controlled trial.

In Phase three, data will be analysed to test the effect of CGT intervention on the scores of baseline and follow-up assessments. All data analyses will be conducted in IBM SPSS Statistics for Windows, version 27.0 (or higher) software. Data will be directly entered into Microsoft Office Excel spreadsheets (version 2202) by investigators and study staff using all standard data management procedures. Descriptive statistics will be calculated according to the normality assumption, with means and standard deviations reported for normally distributed data, and medians and interquartile ranges reported for non-normally distributed data. Within-group comparisons between baseline and follow-up assessments for primary and secondary measurements will be analysed using repeated-measures analysis of variance (ANOVA). In contrast, independent ANOVA will be used for between-group comparisons. For additional explorative analyses, correlation and regression models can be used to analyse the effects of other factors (e.g. age, gender) on the cognitive decline between the baseline and follow-up assessments.

In addition to the primary and secondary outcome analyses, a sub-group analysis will be performed to explore the potential effects of the CGT intervention based on participants’ baseline memory function and executive function. Participants will be stratified into subgroups based on their performance on the cognitive test scores, and the intervention effects will be compared between these subgroups. This exploratory analysis may help to identify which patients are most likely to benefit from the CGT intervention and guide future research in this area.

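### Thirty intervention patients with 20% dropout leave 24 completers, one short of the 25 that the protocol says it ensures; the dropout assumed for controls is not stated

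*Protocol article*

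**What the plan says.** The Phase three numbers stand at the end of the protocol article's Participant withdrawal section. The total is given first: "Fifty-five people attending haemodialysis therapy will be recruited for Phase three". For the intervention arm: "The intervention arm includes 30 patients to account for up to a 20% potential dropout and ensure at least 25 can complete the study". For the control arm: "The control arm will have 25 haemodialysis patients with usual care". Both arms are to be assessed at baseline and again about four months later, with a two-week window either way.

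The Statistical analysis section adds that there is no formal power calculation and says of the sample size that "it is pragmatically determined by the number of eligible patients in our dialysis unit". The results are to inform the sample size of a later, larger trial. Retention is listed among the feasibility outcomes in the Outcomes section.

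**The concern.** The intervention-arm sentence gives a recruitment number, a dropout ceiling and a guaranteed number of completers. A reader who multiplies the first by one minus the second gets 24, not 25. The wording is firm at both ends: "to account for up to a 20% potential dropout" includes 20% itself, and "ensure at least 25 can complete the study" is a floor, not an expectation. As written, the floor fails at a dropout rate that the sentence says it has allowed for.

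The control arm raises a second, lesser question. It has no allowance, yet its patients face the same follow-up and the same right to withdraw.

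What is at stake is the accuracy of a stated sample-size property. Retention is one of the things this pilot is meant to measure, and its results feed the sizing of the definitive trial. The same inflation should not be carried forward: recruiting 1.2 times the required number and then losing 20% leaves 1.2 × 0.80 = 96% of the completers required.

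**Working it through.** **Inputs, all from the Participant withdrawal section**
- Intervention arm recruited: 30
- Dropout allowed for in that arm: up to 20%
- Completers said to be ensured in that arm: at least 25
- Control arm: 25, with no dropout rate and no completer target
- Total recruited: 55

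**Reproducing the plan's figure.** Multiplying the completer target by one plus the dropout rate gives 25 × 1.20 = 30, exactly the stated number. The article shows no derivation, so this is only a calculation that fits.

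**Forward check.** Completers = recruited × (1 − dropout) = 30 × 0.80 = 24. This is 25 − 24 = 1 below the stated floor.

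**Solving for each figure with the other two held fixed**
- Dropout that 30 recruits can bear and still leave 25: (30 − 25)/30 = 5/30 = 16.7%.
- Recruits needed for 25 completers at 20% dropout: 25/(1 − 0.20) = 31.25, rounded up to 32. Check: 32 × 0.80 = 25.6.
- Completers from 30 recruits at 20% dropout: 24.

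**Chance of reaching 25.** This takes each patient to drop out independently with the same probability, which is an assumption.

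| Dropout | Expected completers of 30 | P(at least 25 of 30) | P(at least 25 of 32) |
|---|---|---|---|
| 10% | 27.0 | 0.93 | 0.99 |
| 15% | 25.5 | 0.71 | 0.90 |
| 16.7% | 25.0 | 0.62 | 0.85 |
| 20% | 24.0 | 0.43 | 0.70 |

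At the stated ceiling, 30 recruits reach 25 completers less often than not. Even 32 recruits do not ensure 25; they only make the expected number exceed it. The verb in the protocol is therefore stronger than any calculation of this kind supports.

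**Control arm.** 30 + 25 = 55, the stated total to be recruited. The control 25 is therefore a number recruited, not a number expected to complete. The article gives no control dropout rate, so the following are illustrations under assumed rates:
- 10%: 25 × 0.90 = 22.5
- 15%: 25 × 0.85 = 21.25
- 20%: 25 × 0.80 = 20

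In whole patients, that is about 22, 21 or 20.

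**The case against.** **This is a pilot, and nothing inferential depends on the figure.** This stands as a limit on importance. The Statistical analysis section disclaims any power calculation, so no power, alpha or detectable effect depends on 25 completers. It does not make the sentence right, because the protocol chose to state a completer floor and its own inputs do not deliver it.

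**Twenty per cent is a ceiling, not a forecast.** This is true. With dropout at or below 16.7% the expected number of completers is 25 or more. The section also keeps participants in follow-up unless they withdraw fully, so a patient who stops using the app need not miss the four-month assessment. But the sentence claims to cover losses up to the ceiling, and at the ceiling it fails.

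**The control arm contradicts nothing.** This stands. Without a stated rate or completer target for controls there is no figure to get wrong. Controls have no app regimen to abandon, so a smaller allowance could be deliberate. The article gives no reason either way, so a request for clarification is all that is warranted.

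**Stronger readings that the article does not support.** A reader might infer that the comparison will rest on 24 + 20 = 44 completers where 50 were promised. That carries the intervention-arm ceiling over to the controls as if it were their expected rate, and the protocol nowhere states 50. A reader might also see a conflict between a size set by the eligible patients in the unit and a fixed target of 55. The two are compatible: the available pool can limit the total while a retention allowance explains the split, and no eligible count is given that differs from 55. Nor should the protocol be asked for a confidence-interval width at 24 against 20. That figure would rest on an assumed control loss, and a calculation that treats patients as independent would ignore the allocation of whole dialysis routes described under Randomisation.

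**Conclusion.** The intervention-arm sentence is wrong as written. Its figures of 30 recruits, up to 20% dropout and at least 25 completers are mutually inconsistent, by one completer (24 against 25), by two recruits (30 against 32), or by 3.3 percentage points of dropout (16.7% against 20%). This follows from the protocol's own numbers by simple arithmetic. Only the probabilities of reaching 25 need a further assumption, that of independent dropout at a common rate.

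The control-arm point is an unexplained asymmetry. It rests on the 25 being a recruitment number, which the total of 55 confirms. Any number of control completers is conditional on a dropout rate that the article does not give.

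The practical effect is small, and the case for correcting the text is that the statement is plainly checkable and costs nothing to put right.

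**What to change.** Keep 30 and correct the sentence in the Participant withdrawal section along these lines: *Thirty patients will be recruited to the intervention arm; at 20% dropout about 24 would complete, and at least 25 would complete only if dropout is at most 16.7%.* Recruiting 32 would also bring the expected number above 25 at 20% dropout, but the protocol says the size is limited by the eligible patients in the unit, so rewording is the practical course.

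Add one sentence for the control arm giving the dropout assumed for it and the completers that this leaves from 25, with the reason if the assumed rate differs from that of the intervention arm.

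The cost is two sentences of text. Recruitment, the analysis and the trial's conduct do not change; one stated figure becomes slightly less favourable.
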